## 1.13 Comparator Vaccine

### 1.13.1 *Rationale for use of a comparator vaccine*

Having a comparator vaccine is particularly useful in phase 1 trials conducted in endemic areas, since background immunity and natural exposure to hookworm infection may otherwise make it difficult to interpret immunogenicity data. The use of a control group will permit comparison of immune responses between those vaccinated with *Na*-GST-1 and those not vaccinated with this antigen, and will result in a clearer interpretation of immunogenicity results. Although a placebo control group would accomplish the same goal, using a comparator vaccine that is beneficial to the participants increases the benefit-risk ratio, which is always relatively low in phase 1 trials.

Furthermore, the use of a comparator vaccine in a blinded study reduces potential investigator bias in reporting adverse events or attributing their causality. It will also safeguard against the probability that an excess of adverse events will be reported in this trial in comparison to an equivalent trial conducted in the United States. From prior experience conducting other trials at this study site, there will be many reported adverse events that are unrelated to the study

interventions: this rural population has reduced access to medical care and performs excessive heavy labour compared to an urban population or one living in the developed world. Thus, this population has significantly more medical afflictions than would be expected in a study population in the United States. Having a comparator arm in the study enables a fairer assessment of whether or not the rate of adverse events is “normal” or not, since to a reviewer unfamiliar with the study site, viewing the number of adverse events might otherwise lead to an erroneous – and negative – assessment of the vaccine’s safety.

### ***1.13.2 Rationale for use of the Hepatitis B vaccine as a comparator***

We have chosen the Butang® hepatitis B vaccine (Instituto Butantan, São Paulo, Brazil) as the comparator vaccine for five principal reasons: (1) it is likely to confer some benefit to the participants receiving it, (2) it has an established safety record, (3) it is a yeast-derived recombinant protein adsorbed to an aluminum-containing adjuvant, (4) it has the same physical appearance as *Na*-GST-1 adjuvanted with Alhydrogel, and (5) its dosing schedule permits easy incorporation into the study design. Furthermore, Butang® is the most widely-used hepatitis B vaccine in Brazil, with over 15 million doses distributed annually.

Available data suggest that most adults living in rural Brazil have not received a primary series of immunizations for hepatitis B. In Brazil as a whole, routine hepatitis B vaccination for infants began in 1996 when it was incorporated into the country’s Expanded Program for Immunization. It is likely that many adults living in Americaninhas have not yet received this vaccine. Although data from the study area on the seroprevalence of markers of hepatitis B infection are scarce, one study of army conscripts from the northeastern part of the state of Minas Gerais (in which the study site is located) revealed a seroprevalence of 3.9% for hepatitis B surface antigen (HBsAg). However, even though a proportion of potential study participants may have been exposed to hepatitis B and have developed antibodies to HBsAg, vaccination of immune individuals poses no safety hazards.

## **2 OBJECTIVES**

### **2.1 Primary Objective**

1. To determine the frequency of vaccine-related AEs, graded by severity, for each dose and formulation of *Na*-GST-1.

### **2.2 Secondary Objectives**

1. To determine the dose and formulation of *Na*-GST-1 that generates the highest IgG antibody response at Day 126, as determined by an indirect enzyme-linked immunosorbent assay (ELISA).
2. To assess and compare the duration of antibody response to *Na*-GST-1.
3. To perform exploratory studies of the cellular immune responses to the *Na*-GST-1 antigen both before and after immunization.

## **3 STUDY SITES**

The study will be conducted in two parts as outlined in **Section 4** below. The first part of the study will be conducted in healthy adult volunteers without history of hookworm infection at the

Centro de Pesquisas Rene Rachou (CPqRR) in Belo Horizonte, Minas Gerais, Brazil. Belo Horizonte is a large city of approximately 4-5 million inhabitants. Although there are parts of the city where residents live in crowded conditions without access to adequate clean water and sanitation and where transmission of hookworm and other soil-transmitted helminths may occur, the majority of people living in this urban center have not been exposed to or infected with these parasites. The CPqRR is a research institution that is part of the Fundação Oswaldo Cruz (FIOCRUZ) network that is the division of the Brazilian federal Ministry of Health dedicated to conducting research on issues of importance to the health of Brazilians.

The second part of the study will be conducted in Americaninhas, a town located in the Municipality of Novo Oriente de Minas, 500 km northwest of Belo Horizonte, the capital of the Brazilian state of Minas Gerais. The Brazilian Fundação Nacional de Saude (National Health Foundation) estimates that there are 1000 people living in the urban municipal center of Americaninhas, with another 4000 living in the surrounding rural areas. The area is hilly and characterized by a tropical altitude climate, with an average temperature of 24°C, and experiences a long rainy season between November and March; annual rainfall is 1300-2000mm. The majority of inhabitants are involved in rural subsistence farming, growing mainly coffee, manioc and beans. Cattle ranching is another important source of income. Houses are predominantly made from concrete or from a combination of wood and mud and have either tiles or iron sheets for roofing. Only approximately 50% of these homes have a latrine and people commonly collect their water from local springs. There is only one health post in the area staffed by two auxiliary health workers who are paid by the municipality.

Americaninhas has been chosen as a site for testing hookworm vaccines based on prevalence surveys conducted over the past few years, and the good working relationship that has been established between the research staff, the local health authorities, and the community.

Starting in 2004, epidemiological studies have been conducted by the study team in the town of Americaninhas and surrounding areas in order to identify the populations at greatest risk for heavy hookworm infection and to conduct post-treatment hookworm re-infection studies in order to inform the sample size calculations for phase 1 and phase 2 studies in the region. These studies have been challenging because of a number of physical challenges including the isolation of the region, the hilly terrain, and the large distances between dwellings. Geographic Information System/Remote Sensing identified high levels of vegetation as a critical feature of the infection sites. Overall, the force of infection in Minas Gerais is high. It was estimated that post-treatment hookworm infection occurs in approximately 300 per 1,000 individuals per year, which represents a level of transmission that is comparable to other areas considered to have intense or high transmission, such as in East Africa. The overall prevalence of *N. americanus* hookworm infection is approximately 68 percent, with approximately one-half of the population also infected with *Ascaris lumbricoides* and with *Schistosoma mansoni*. As in other regions of the world, the prevalence of hookworm infection rises in the first 5 years of life when it reaches a plateau. In addition, the intensity of hookworm infection (as measured by fecal egg counts using the Kato-Katz technique) also rises until the age of 5 years and then remains high. A second increase in hookworm intensity occurs after the age of 50.

## 4 STUDY DESIGN

### 4.1 Overall Design

The study will be conducted in two parts (**Table 1**). **Part I** of the study will be an open-label dose-escalation phase 1 trial of *Na*-GST-1/Alhydrogel® administered with or without GLA-AF conducted in Belo Horizonte in healthy adult volunteers without history of hookworm infection. **Part II** will be a randomized, controlled, double-blind phase 1 dose-escalating clinical trial in healthy adult volunteers living in the hookworm-endemic area of Americaninhas. This part of the study is designed to evaluate the safety, reactogenicity, and immunogenicity of *Na*-GST-1/Alhydrogel® with or without GLA-AF, as compared to Butang® hepatitis B vaccine.

Safety parameters will be monitored throughout both parts of the study. The primary immunological endpoint for both parts will be the measurement of the antigen-specific antibody response.

Prior to beginning study-related activities in Americaninhas in Part II of the study, the consent and cooperation of representative community members will be sought, after which volunteers will be invited to participate in the study. In both Belo Horizonte and Americaninhas, after providing written informed consent and passing the informed consent comprehension questionnaire, volunteers will undergo eligibility screening, including a complete medical history, physical examination, hematology and coagulation testing, serum glucose testing, liver and renal function testing, HIV antibody testing, Hepatitis B and C serology, and urinalysis; urine pregnancy testing will be performed on all female volunteers. In addition, all volunteers will be tested for serum IgE antibodies to *Na*-GST-1, and a fecal examination will be performed for ova and parasites. All clinically significant abnormalities will be reviewed with volunteers and referral for follow-up care will be provided. After screening, those volunteers determined to be eligible, based on the inclusion and exclusion criteria described in **Section 5** in this protocol, will be invited to participate in the study.

Dose cohorts will be enrolled and vaccinated in a consecutive fashion as described in **Section 4.3**. In **Part I** of the study, 36 volunteers will be enrolled into one of six cohorts (see **Table 3**): in the first cohort, 6 individuals will receive the 10 µg dose of *Na*-GST-1/Alhydrogel®; in the second cohort, 6 individuals will receive the 10 µg dose of *Na*-GST-1/GLA-AF; in the third and fourth cohorts, 6 volunteers each will receive 30 µg *Na*-GST-1/Alhydrogel® and *Na*-GST-1/Alhydrogel®/GLA-AF, respectively; while in the fifth and sixth cohorts, 6 volunteers each will receive 100 µg *Na*-GST-1/Alhydrogel® and *Na*-GST-1/Alhydrogel®/GLA-AF, respectively. Enrollment of these cohorts will be staggered by (at least) one-week intervals: Cohorts 2 and 3 will be enrolled and begin vaccinations at least 1 week after Cohort 1, Cohorts 4 and 5 will be vaccinated at least 1 week after Cohorts 2 and 3, and Cohort 6 will be vaccinated at least 1 week after Cohorts 4 and 5.

In **Part II** of the study, 66 volunteers will be progressively enrolled into one of six dose cohorts. In the seventh, ninth and eleventh cohorts, volunteers will be randomized to receive either *Na*-GST-1/Alhydrogel® (n=8) or Butang® (n=2), while in the eighth, tenth and twelfth cohorts, volunteers will be randomized to receive either *Na*-GST-1/Alhydrogel® (n=2) or *Na*-GST-

1/Alhydrogel®/GLA-AF (n=10). Volunteers randomized to receive *Na*-GST-1 will receive either the 10 µg, 30 µg or 100 µg dose, as outlined in **Table 3**.

As with other aluminum hydroxide-adsorbed vaccines, hypersensitivity reactions would be expected to occur within the first 24 hours after receipt of either of the two vaccines, and other severe local or systemic reactions within 72 hours of vaccination. Participants will therefore be observed for immediate reactions following each vaccination for at least 2 hours, and will have a clinical assessment either in their home or at the study clinic on Days 1, 3, 7, and 14 following each vaccination. See **Tables 2** and **3** for tabular descriptions of the vaccination schedule for all dose cohorts, as well as **Section 7.6** and **Appendix B** for a detailed description of the scheduled clinical and laboratory evaluations.

Prior to enrolling and vaccinating volunteers in Part II of the study, safety data up to and including Day 70 post-vaccination from the sixth cohort (i.e., the cohort administered 100 µg *Na*-GST-1/Alhydrogel®/GLA-AF) will be reviewed by the Safety Monitoring Committee (SMC). The trial will not proceed to Part II of the study if any of the stopping criteria listed in **Section 8.5** are met, or if in the clinical judgment of the SMC, continued enrollment and vaccinations would pose an unacceptable safety risk to the participants.

In Part II of the study, prior to dose escalation (e.g., after enrolling Cohort 7 but before enrolling Cohort 9), safety data up to and including Day 7 post-vaccination will be compiled from the lower dose cohort for review by the Medical Monitor and/or SMC. The trial will not proceed to the next dose cohort if any of the stopping criteria listed in **Section 8.5** are met or, in the clinical judgment of the SMC and/or Medical Monitor, the next higher dose would pose an unacceptable safety risk to the participants.

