| 0                                          | Vaccination 1
(Day 0)                                                                                                                      |                                                                                                                                                                                                          |                                                                                                                                                |                                                                                                                                                                                                             |                                                                                                                                                  |                                                                                                                                                                                                               |
| 2                                          |                                                                                                                                               | Vaccination 1
(Day 0)                                                                                                                                                                                 | Vaccination 1
(Day 0)                                                                                                                       |                                                                                                                                                                                                             |                                                                                                                                                  |                                                                                                                                                                                                               |

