## 4.2 Sample Size and Estimated Duration of Study

A total of 102 participants will be enrolled (see **Section 10.2** for a justification of the sample size). Forty-eight will receive *Na*-GST-1/Alhydrogel® (one of three dose concentrations), 48 will *Na*-GST-1/Alhydrogel®/GLA-AF (one of three dose concentrations), and 6 will receive Butang® hepatitis B vaccine. The trial is expected to last for a total of 24 months. Each participant will be followed for 16 months from the time of the first injection.

In Part II of the study, in order to ensure that the vaccine formulations will be evaluated in individuals recently infected with hookworm, at least 4 individuals will be enrolled into each of Cohorts 7-12 who were infected with hookworm based on the fecal exam conducted during the

screening for the study, or who had a documented infection within 3 months of the date planned for the first vaccination for the participant.

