### 4.3 Group Allocation

Dose cohorts will be enrolled consecutively. In **Part I** of the study, within Cohort 1 all participants will receive the 10 µg dose of *Na*-GST-1/Alhydrogel®; within Cohort 2, all will receive 10 µg of *Na*-GST-1/Alhydrogel®/GLA-AF, and so on. In **Part II** of the study, within Cohorts 7, 9 and 11 of 10 participants, 8 will be randomly assigned to receive *Na*-GST-1/Alhydrogel® and 2 to receive Butang® (see **Section 7.3**). Within Cohort 7, Cohort 9, and Cohort 11, those randomized to receive *Na*-GST-1/Alhydrogel® will receive a dose containing 10 µg, 30 µg and 100 µg of *Na*-GST-1, respectively. Also in Part II of the study, within Cohorts 8, 10, and 12 of 12 participants, 2 will be randomly assigned to receive *Na*-GST-1/Alhydrogel® and 10 to receive *Na*-GST-1/Alhydrogel®/GLA-AF. Within Cohorts 8, Cohort 10, and Cohort 12, participants will receive a dose containing 10 µg, 30 µg and 100 µg of *Na*-GST-1, respectively.

In both **Part I** and **Part II** of the study, 1 or 2 additional eligible volunteers above the number to be enrolled in a given cohort may be scheduled for a Day 0 visit, if possible. On the day of first vaccination, the first volunteers who arrive at the study clinic will be evaluated for continued eligibility and vaccinated in the order that they arrive; the additional eligible volunteers will be kept as alternates if some of the first arrivals cannot be vaccinated on the day of first vaccination (i.e., due to pregnancy, withdrawal of consent, etc.). If the alternates are not vaccinated, they will be invited to participate as members of the next dose cohort. Those alternates for the final cohorts in both Part I and Part II who are not vaccinated and therefore not enrolled in the study, will be offered vaccination with a non-study, licensed vaccine such as the tetanus toxoid or influenza vaccine.

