### 4.4 Blinding

**Part I** of the study will be an open label phase 1 trial. In **Part II**, investigators and participants will be blinded as to an individual study participant's allocation to either *Na*-GST-1/Alhydrogel®, *Na*-GST-1/GLA-AF or Butang® vaccine until all participants have completed their Day 140 visit, the safety and primary immunogenicity data have been monitored and entered into the database, and the database has been locked. Only the study vaccine manager (and potentially an assistant) will be aware of the participants' vaccine allocation. The study vaccine manager will refer to the unique randomization code assigned to that participant to determine the assigned vaccine for each participant (see **Section 7.3**). Vaccine will be prepared by the study vaccine manager in a separate room and the vaccine-filled syringes will be handed to the vaccinator(s). Since the 10 and 30 µg doses of the *Na*-GST-1 formulations are of different volumes (0.1 ml and 0.3 ml, respectively) than that of Butang® (1.0 ml), the contents of all syringes will be disguised using opaque tape. As a further precaution, the vaccinator(s) will not be based in Americaninhas and will not be involved in assessments of reactogenicity or adverse events.

Due to the staggered, dose-escalation design of Part II of the trial, it will not be possible to blind to the dose of *Na*-GST-1 that an individual may have received. That is, those participants

assigned to Cohort 7 may receive either the 10 µg dose of *Na*-GST-1/Alhydrogel or the Butang® vaccine, whereas Cohort 8 will receive either 10 µg *Na*-GST-1/Alhydrogel or *Na*-GST-1/GLA-AF, Cohort 9 will receive either 30 µg *Na*-GST-1/Alhydrogel or Butang®, and Cohort 10 will receive either 30 µg *Na*-GST-1/Alhydrogel or *Na*-GST-1/GLA-AF, and so on. Since Cohorts 9 and 10 will receive their vaccinations after Cohorts 7 and 8 (see **Table 3**) and Cohorts 11 and 12 will receive their vaccinations after Cohorts 9 and 10, it will not be possible to blind to the dose of *Na*-GST-1 that may have been given, only to the allocation between *Na*-GST-1/Alhydrogel, *Na*-GST-1/GLA-AF, or Butang®.

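### Part II is described as randomised and double-blind against Butang for both formulations, but GLA-AF versus Butang is a cross-cohort comparison that is neither randomised nor blinded

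*Protocol*

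**What the plan says.** Section 4.1 states that Part II "will be a randomized, controlled, double-blind phase 1 dose-escalating clinical trial in healthy adult volunteers" and that it is meant to assess Na-GST-1/Alhydrogel "with or without GLA-AF, as compared to Butang ® hepatitis B vaccine". Section 4.4 says that in Part II "investigators and participants will be blinded as to an individual study participant's allocation to either" Na-GST-1/Alhydrogel, the GLA-AF formulation or Butang. It adds that dose cannot be masked but that allocation among the three vaccines is.

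The allocation is fixed inside each cohort:

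- Section 4.3, Cohorts 7, 9 and 11 (10 participants each): "8 will be randomly assigned to receive *Na*-GST-1/Alhydrogel ® and 2 to receive Butang".
- Section 4.3: "within Cohorts 8, 10, and 12 of 12 participants, 2 will be randomly assigned to receive" Na-GST-1/Alhydrogel and 10 the GLA-AF formulation. Section 4.1 agrees: "while in the eighth, tenth and twelfth cohorts, volunteers will be randomized to receive either" one or the other.
- Section 4.2, overall: "6 will receive Butang ® hepatitis B vaccine".

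Section 4.3 enrols cohorts one after another, and no randomisation between cohorts is described. In section 7.3 volunteers come to enrolment already assigned to a cohort. Exclusion 27 in section 5.2 (a prior primary hepatitis B vaccine series) applies to Cohorts 7, 9 and 11 only.

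Section 10.1.1 plans to pool all Butang recipients and compare them with each dose and formulation, GLA-AF included. AE incidence is compared between cohorts rather than inside them. The antibody analyses also combine recipients of the same vaccine across cohorts, and a possible longitudinal model would explore differences among all three vaccines.

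**The concern.** A reader of 4.1 and 4.4 would take any Part II comparison with Butang to be protected by randomisation and blinding. For GLA-AF it has neither protection.

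Section 1.13.1 gives two reasons for a comparator vaccine: to separate vaccine responses from background exposure and background illness, and, because the study is blinded, to limit investigator bias in reporting AEs and judging their cause. For GLA-AF versus Butang the second reason is lost, and the first rests on two cohort types being comparable although their eligibility rules differ.

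The primary objective concerns vaccine-related AEs, so causality judgement enters the endpoint directly. Under 9.2.1, the report after Day 140 informs whether to proceed to children and with which formulation. If a GLA-AF versus Butang difference appears there as a randomised double-blind result, it will be given more weight than the design supports.

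**Working it through.** **1. Reproduce the plan's totals.** Inputs are the cohort sizes in Table 1 and section 4.3.

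| Part II cohorts | Alhydrogel | GLA-AF | Butang |
|---|---|---|---|
| 7, 9, 11 (each) | 8 | 0 | 2 |
| 8, 10, 12 (each) | 2 | 10 | 0 |
| Sum over all six | 3×8 + 3×2 = 30 | 3×10 = 30 | 3×2 = 6 |

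The Part II total is 30 + 30 + 6 = 66, as stated. Part I adds 18 Alhydrogel and 18 GLA-AF, giving 48 + 48 + 6 = 102, also as stated. Part I is open-label and has no Butang. (Section 10.1.1 gives 8 hepatitis B recipients where sections 4.2 and 4.3 and Table 1 give 6. The 6 is used here.)

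**2. Which pairs share a randomisation?**

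- Alhydrogel versus Butang: three cohorts, 24 versus 6.
- GLA-AF versus Alhydrogel at the same dose: three cohorts, 30 versus 6.
- GLA-AF versus Butang: no cohort, 0 of 30 versus 0 of 6.

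**3. Which pairs share a blind?** Section 4.4 itself lists what each cohort may receive. Anyone who knows that a participant is in Cohort 8, 10 or 12 knows that Butang was not given. Anyone who knows the cohort is 7, 9 or 11 knows that GLA-AF was not given. The chance that a participant received investigational vaccine is 12/12 = 100% in the first set and 8/10 = 80% in the second.

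**4. Are the cohort types alike apart from vaccine?** Not by rule. A person with a prior primary hepatitis B series can enter Cohorts 8, 10 and 12 but not 7, 9 and 11.

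**5. What do the randomised contrasts offer?** Alhydrogel at the same dose is in both cohorts of each dose level. So (GLA-AF − Alhydrogel) + (Alhydrogel − Butang) is an indirect estimate built only from within-cohort contrasts. With a common per-participant variance σ², per dose:

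- Indirect: 1/10 + 1/2 + 1/8 + 1/2 = 1.225σ².
- Planned pooled comparison, one GLA-AF dose versus all Butang: 1/10 + 1/6 = 0.267σ².
- For scale, a hypothetical direct randomised 10 versus 2: 1/10 + 1/2 = 0.6σ².

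The indirect variance is 1.225/0.267 ≈ 4.6 times that of the pooled comparison. Averaged over the three doses it is 1.225/3 = 0.408σ², against 1/30 + 1/6 = 0.2σ² for all GLA-AF versus all Butang. The pooled comparison is tighter because it gives up the protection of randomisation.

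**The case against.** The structure is not hidden. Section 4.4 sets out what each cohort may receive, and 10.1.1 says that comparisons run between cohorts. The primary objective is the AE frequency for each dose and formulation, which needs no Butang contrast. Section 10.2 disclaims power. All of this stands and limits the point to what is claimed for the comparison. It does not make the wording of 4.1 and 4.4 correct, and low power is a separate matter from bias.

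Section 8.2.3 classes every injection-site reaction as definitely related, so an assessor's knowledge of the cohort cannot change causality for those events. That also stands. What remains exposed is causality for systemic and laboratory events, and reporting and grading that depend on judgement.

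Some stronger readings are tempting but not supported:

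- A reader might infer that GLA-AF recipients have no randomised control. They have a blinded one, Na-GST-1/Alhydrogel at the same dose, with 2 per cohort and 6 in all. It isolates the adjuvant's added effect.
- A reader might infer that no analysis can draw on randomisation for GLA-AF versus Butang. The indirect, cohort-stratified estimate does, although imprecisely.
- A reader might treat GLA-AF as the only first-in-human component. Section 1.9 says the same of Na-GST-1.
- Table 3 starts Cohorts 8 and 9 in the same week, and Cohorts 10 and 11 likewise, so a reader might infer that each pair should share one randomisation list. The table's footnote calls the times approximate and the intervals minimums. A blinded joint list would hide the dose cohort on which suspension criteria c and d (8.5) and the safety committee's review (8.4.2) rely. It would also complicate the quota of recently infected participants per cohort (4.2), and would cut the chance of Butang in Cohorts 9 and 11 from 2/10 = 20% to 2/22 = 9%.

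**Conclusion.** The protocol claims a property that its allocation does not have. Two of the three vaccine pairs in Part II are randomised and blinded. GLA-AF versus Butang is neither: 0 of 30 GLA-AF recipients share a list or a blind with any of the 6 Butang recipients, and the cohort types differ by an eligibility rule.

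The counts rest on the cohort table alone. The statement about blinding assumes that study staff know the cohort, which 4.4 accepts when it says dose cannot be masked. The variances assume equal σ² in all arms and are only a guide for binary AEs. The indirect estimate further assumes that the Alhydrogel versus Butang effect carries from one cohort to the other at the same dose.

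The documents do not show that the cross-cohort comparison is biased, or in which direction. They show only that randomisation and blinding do not protect it. The design itself need not change.

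**What to change.** - **Sections 4.1 and 4.4:** state that Na-GST-1/Alhydrogel versus Butang is randomised and blinded within Cohorts 7, 9 and 11, that GLA-AF versus Na-GST-1/Alhydrogel at the same dose is randomised and blinded within Cohorts 8, 10 and 12, and that GLA-AF versus Butang is neither.
- **Section 10.1.1:** label the pooled GLA-AF versus Butang comparison, for AEs and for antibody, as non-randomised and descriptive. Report beside it the two sets of within-cohort contrasts, stratified by cohort. The indirect GLA-AF versus Butang estimate may be added with its confidence interval and a note on its imprecision.

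The cost is a little more analysis and a less favourable description of one comparison. Cohort sizes, randomisation lists, eligibility, visits and escalation are untouched.
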